	What factors will influence sustainability of training and knowledge translation for GPs, AHPs and community pharmacist?	In-depth interviews of GPs and AHPs as above Pre- and post surveys of AHPs who participate in the workshops AHP planning strategies document from the workshops
	What is the GPs professional network in relation to fall prevention and who is influential within their network?	Relational network (who and influence) questions in survey for trial GPs. Network influence question in AHPs survey and in the ecological survey of GPs in geographical area of SNPHN
	How effective is iSOLVE dissemination across the SNPHN network?	Geographical survey of GPs in SNPHN

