#### Data analysis plan

Data analysis will be on an intention-to-treat basis. For the primary analysis of falls, negative binomial regression will be used to compare the total number of falls per person in the two groups, using an offset for exposure time and accounting for clustering. GP engagement in fall prevention management and GP referral practices will be assessed using questions 11 and 12, respectively, of the 12-month GP survey and corresponding questions on the baseline survey. For management, a score from 0 to 3 will be allocated to each of the first three items and summed to give a total out of 9. The total score for each GP at 12 months will be compared between groups using regression analysis with baseline score as a covariate and adjusting for clustering by GP practice. For referral practice, the number of types of practitioners (out of 13 possible) to whom a GP sometimes or often refers older patients at risk of falling will be counted. The change from baseline for each GP will be compared between groups using Poisson regression, adjusting for clustering by GP practice. Change in Drug Burden Index will be calculated for each patient and compared between groups using regression analysis, controlling for any baseline differences in risk factors (age, gender, comorbidities, hospitalization in past year, and use of walking aid) and accounting for clustering.

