#### In-depth interviews and surveys

The process of understanding implementation of the trial is iterative, seeking explanatory data at all layers, and over the entire time, of the intervention. Initial process evaluation will involve gathering data synchronistically with the intended intervention. Data will include surveys, in-depth interviews, observations and field notes, and documentation of meetings. Guided by NPT, we will examine the “coherence” of the proposed change for those in the work setting and how to facilitate the “collective action” needed to implement changes in practice, as follows:General practices. Data will comprise documentation of the academic detailing process and in-depth interviews with a sample of GPs and practice nurses participating in the intervention cluster. The aim is to elucidate how they perceive fall prevention as an issue for their patients; the barriers and facilitators to falls identification and to implementing fall management and referral practices; and how the iSOLVE resources are used (or not) and the perceived value of the education package and resources to changing practice.Allied Health Professionals (AHPs). AHPs are recruited to the workshops primarily thorough the SNHN website and newsletter. Other strategies have included professional association websites and interest groups, a Google™ search of service directories and service providers identified from GPs. AHPs are eligible if they are located in the geographical area of the SNHN, provide community services, provide or intend to provide fall prevention services to older people, and are able to receive GP referrals. A pre-, 3-, and 12-month post-workshop survey is administered following AHP education sessions and in-depth interviews conducted with a sample of AHPs participating in the workshops. The AHP implementation planning strategies compiled from data collected at the workshops will be used as an additional data source. The surveys include a combination of open-ended and Likert scale response questions; practice change, frequency of assessment and interventions related to fall prevention, referral patterns (to/from), type of services offered, and level of confidence in related skills. Demographic questions record profession, service sector, and nature of employment status. The interviews will ascertain the views of AHPs on any changes (or not) in the referral process; how effective the referral process is, and the factors affecting adoption and implementation of the intervention.

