#### Survey across geographical area

A survey will be used to evaluate GP referral patterns and practices as markers of uptake and implementation across the intervention region, that is, the SHPHN. The survey comprises the same questions as in the trial survey for participating GPs Trends in program perceived efficacy, adoption, and implementation [40, 41] will be monitored over the 5 years of the program. The survey is being distributed annually to all GPs via the SNPHN mail lists in electronic format. As response rates are usually low for GPs [4], we are also randomly selecting 10% of all GPs in the region and mailing them a hard copy of the survey with pen. The random sample was selected using a computer-generated random permutation of integers.

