#### Implementation data analysis: surveys, observation data, and interviews

The information gathered will be used as indicative and descriptive information to inform further dissemination. Responses to survey data will be coded and compared within group and over time. Data will be explored using descriptive and graphical methods and, where possible, measure change in knowledge or practice using independent sample t tests and multinomial logistic regression. Documentation relating to the intervention (e.g., minutes of meetings, discussions with stakeholders) will be examined using content analysis. Analysis will focus on the “work of the intervention” [47]—how doing the work, concerns raised about the work, and how responsibility for falls prevention strategies is distributed across different groups. All interviews will be audio-recorded and transcribed verbatim. Thematic analysis (developing codes) will identify patterns within and across the study groups [48]. A combination of inductive and deductive coding will be used—coding will commence with examination of barriers and facilitators, but will be open to unexpected findings that may contribute to these. Data analysis will examine similarities and differences within and between stakeholder and participant groups and changes evident at different time points in the intervention [49].

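### The implementation surveys are to be tested for change with independent-sample t tests whatever their design, which is the wrong test for the repeated allied-health survey

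*Protocol article*

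**What the plan says.** The article's section on implementation data analysis gives one set of methods for the surveys: "Responses to survey data will be coded and compared within group and over time". After descriptive and graphical work, and as far as the data allow, it will "measure change in knowledge or practice using independent sample t tests and multinomial logistic regression". No paired test, mixed model or other allowance for repeated answers is named for these surveys. The same paragraph sets their status: "The information gathered will be used as indicative and descriptive information to inform further dissemination".

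That paragraph covers surveys of different designs.

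- **Allied health professionals** (In-depth interviews and surveys): "A pre-, 3-, and 12-month post-workshop survey is administered following AHP education sessions". Table 2 lists these as "Pre- and post surveys of AHPs who participate in the workshops" and uses them as one of three sources for the question on sustainability of training. The content is "practice change, frequency of assessment and interventions related to fall prevention, referral patterns (to/from), type of services offered, and level of confidence in related skills". No comparison group of allied health professionals is described.
- **Area GPs** (Survey across geographical area): "The survey is being distributed annually to all GPs via the SNPHN mail lists in electronic format". A 10% random sample is also mailed a paper copy. Nothing says that respondents are linked from year to year.

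The trial GPs' survey is handled separately, in the data analysis plan of the effectiveness trial. There the 12-month management score is "compared between groups using regression analysis with baseline score as a covariate and adjusting for clustering by GP practice".

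**The concern.** An independent-sample t test assumes that the two sets of answers come from different people. In the allied-health survey they come from the same people at different times, and the stated comparison is within group and over time. Two things can then go wrong.

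First, the test ignores the correlation between a person's own answers. When that correlation is positive, the standard error is too large and a real change in practice or confidence is easier to miss.

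Second, an unlinked comparison can set everyone who answered before the workshop against the smaller group who answer later. If the more engaged professionals are the ones who reply at 12 months, the wave means differ even though nobody has changed.

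At stake is the quantitative reading of whether the workshops changed allied-health practice. The article describes a hybrid design that weights implementation and effectiveness equally, so this deserves a suitable method even though it is not the falls outcome.

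**Working it through.** **Inputs.** From the protocol article: three waves (pre, 3 and 12 months), workshop attendees at each wave, comparison within group over time, independent-sample t test. The article gives no allied-health sample size, SD, within-person correlation or survey response rate, so there is no stated figure to reproduce. Assumed here: n = 50 to 200 people, ρ = 0.3, 0.5 or 0.7, true change d = 0.3 or 0.4 SD, two-sided 5% level, equal variances. Steps 1 to 3 also assume that everyone answers both waves.

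**1. Standard error.**
- Used by the independent test: SD × √(2/n).
- Correct for the same people twice: SD × √(2(1−ρ)/n).
- Ratio: 1/√(1−ρ), that is 1/√0.7 = 1.20, 1/√0.5 = 1.41, 1/√0.3 = 1.83.

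**2. Actual error rate (n = 50, ρ = 0.5).**
- Rejection threshold: 1.984 × √(2/50) = 0.397 SD.
- True standard error: √(2 × 0.5/50) = 0.141 SD.
- 0.397/0.141 = 2.81, a two-sided error of about 0.5% instead of 5% (0.6% by simulation). By simulation it is about 2% at ρ = 0.3 and below 0.1% at ρ = 0.7. The paired test stays at about 5%.

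**3. Power.** For n = 50, d = 0.4, ρ = 0.5: (0.397 − 0.4)/0.141 = −0.02, so power is 51%. For n = 80, d = 0.3, ρ = 0.5: threshold 1.975 × √(2/80) = 0.312, true standard error √(1/80) = 0.112, (0.312 − 0.3)/0.112 = 0.11, so power is 46%.

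| n | d (SD) | ρ | Independent | Paired |
|---|---|---|---|---|
| 50 | 0.4 | 0.3 | 51% | 65% |
| 50 | 0.4 | 0.5 | 51% | 79% |
| 50 | 0.4 | 0.7 | 51% | 95% |
| 80 | 0.3 | 0.5 | 46% | 76% |

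**4. Selective non-response, no true change.** Let r be the later response rate and g the baseline gap in SD between later responders and non-responders. The baseline mean of everyone is the responders' mean minus (1−r)g. Comparing all early answers with the later answers therefore shows a false gain of (1−r)g. With r = 0.5 and g = 0.3 this is 0.5 × 0.3 = 0.15 SD.

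A simulation made a stronger assumption: about 60% retained, with the log-odds of replying rising by 1 per SD of a person's stable score, and ρ of 0.5 or 0.7. The false change was 0.23 to 0.28 SD. The unlinked test rejected in about 12% of runs at the low end (n = 50, ρ = 0.5) and about 76% at the high end (n = 200, ρ = 0.7). The paired test showed a change near 0 and rejected in about 5%.

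Step 4 applies only if all early responders are compared with all later ones. If the comparison is restricted to people who answered both waves, it falls away and steps 1 to 3 remain.

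**The case against.** The strongest reply is that the t-test sentence does not name the allied-health survey. It covers several surveys at once, and for the annual area GP survey, whose respondents are not said to be linked, independent-sample methods are defensible. One sentence may simply list methods without assigning them. This stands as a limit on certainty: a reader might infer a deliberate decision to analyse the allied-health cohort as unpaired, and the article does not say that. But the sentence is not restricted to the area survey, and the allied-health survey is given no other test.

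It can also be said that an independent t test would be valid for change scores compared between subgroups, since profession, sector and employment status are recorded and differences between groups are mentioned. That is possible, but the wording closest to the test is a comparison within group and over time, and no subgroup contrast is named.

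The work is qualified as indicative and done where the data allow, with no significance level, power target or decision rule. That limits the consequence. It does not make the independence assumption true.

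Three further points stand. The drop-out effect presumes a comparison of all early with all later responders, which the article does not specify. Every magnitude depends on assumed inputs. And nothing shows whether surveys can be linked: a code may already exist, or early surveys may be anonymous.

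**Conclusion.** The point holds in a limited form. Independent-sample t tests are named for change across all implementation surveys, and for the allied-health survey, which repeats measurements on one cohort, that is the wrong test. For any positive within-person correlation the standard error is too large, by 20% to 83% for an assumed ρ of 0.3 to 0.7. With complete follow-up the consequence is lost power, not false positives. False change arises only if non-response is selective and the waves are compared unlinked.

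Two stronger readings are not supported. A reader might infer that the trial's main results are at risk. They are not: the falls analysis does not use this test, and the trial GPs' survey analyses use each GP's own baseline and adjust for practice. A reader might also infer that the allied-health findings will be biased. The article gives neither the response rates nor the exact comparison needed to say so.

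The impact is modest, because the analysis is descriptive and sits beside interviews and planning documents as evidence on sustainability.

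**What to change.** State which method applies to which survey.

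- **Allied-health survey, where respondents can be linked:** a mixed model over the three waves with a random intercept per person, or paired tests for pre versus 3 months and pre versus 12 months. For multinomial outcomes, add a person-level random effect or use standard errors clustered on the person.
- **Non-response:** compare the baseline scores of later responders and non-responders. A paired test describes only those who answered both waves, and the mixed model assumes that missing answers are missing at random. This comparison helps the reader judge both.
- **Waves that cannot be linked, such as the annual area GP survey:** keep independent-sample methods, and say when reporting them that the waves were treated as separate samples.

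The cost is a sentence or two in the analysis plan and a respondent code carried across waves. No extra survey items are needed. The downside is that the link may not be recoverable for surveys already completed anonymously. Table 1 refers to professionals who have already attended workshops, so some pre-workshop surveys may be affected.

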## Discussion

The fundamental goal of this research project is to achieve dissemination and planned sustainability of an applied model of delivery integrated processes and pathways to identify older people at risk of falls and engage a whole of primary care approach to fall prevention. The longer term aim is a model that could be used for widespread dissemination. Historically, there have been a number of challenges in implementing prevention programs into primary health. Over the past decade, there have been calls for improved detection of early fall risk, awareness and access to services, and strengthening pathways between referrers and service providers [50].

The advantages of a blended effectiveness-implementation design is that it uses mixed-methods which are designed to evaluate both content and context as a way of accelerating research into practice, in particular by avoiding lengthy step-wise approaches [51, 52]. It also offers a way of optimizing our knowledge and understanding as there is a blending and interaction of both intervention and implementation, and it provides opportunities for triangulation and richly validated findings [53].

At the same time, this approach raises a number of methodological challenges [25]. While core features of design rigor in cluster randomized trials are being adhered to [32], this is a pragmatic trial in which the intervention is being delivered in a real-world setting. We therefore have less control both of intervention fidelity for GPs and also of whether and how the recruited patients follow through with any GP-advised strategies, recommendations, or referrals. Given resources in a hybrid design need to cover a variety of expertise and personnel [25] and the fact that we minimized patient secondary assessment compared to what would be usual in an effectiveness/explanatory trial, there is a limited opportunity to capture, for example, quantitative adherence data and validated measures of participant engagement. Contamination may occur as allied health professionals who attended workshops could see control patients referred to them for other reasons or from other sources, as they have been encouraged to identify people who have fallen or at risk of falls, combined with their new skills to implement fall prevention. There are the usual generalization issues related to cluster randomized trials in defining how included practices (and patients) might differ from those not included [54]. Initial recruitment via newsletters may have included those most keen, and ongoing recruitment has been expanded to include multiple methods. Despite this, so far, we have experienced a high response rate and interest by GP practice indicating fall prevention is a topic of interest to many GPs. While threats to external validity may be heightened in this blended design, we are applying robust trial rigour, will review self-report of patient engagement in fall prevention over the follow-up period, and active dissemination of the GP resources and processes throughout the SNHN will not occur until completion of the cluster randomized trial.

As an implementation project, the context of one geographical area may well be different from others, such as rural versus metropolitan, thus introducing an effect modification. Willis et al. [55] warn how intentions for embedded strategies into existing services can be hindered by a reliance on material resources for continuation rather than embedding the processes based on key features for sustainability. Further, we know that training is a crucial and necessary first step in the process of change [56] but much more needs to be understood about how change occurs and what planning is needed [57]. Our expectation is that the qualitative analysis approach using Normalization Process Theory will give the necessary depth of understanding to the contextual issues related to implementation and sustainability. This should enable us to place appropriate emphasis on the lessons we will learn, what the key drivers for change are and what can be generalized, or what will need further research.

While challenges exist, there is potential for significant outcomes as the iSOLVE pathways project brings together practice and research to collectively solve a major national problem with implications for policy service delivery. The project outcomes will be a multi-disciplinary pathway model for fall prevention that will have been tested empirically in an urban area. It will provide evidence of resource need and allocation, and feasible processes and guidelines for fall identification and prevention in general practice and community-based healthcare practices. Practical outcomes include training modules and processes as well as a model for organizational and system support needs for implementation and sustainability of GP and allied health evidence-based practice in falls prevention. Partnerships with regional, state, and professional organizations provide opportunities for widespread dissemination, leadership, and diffusion.
